#### (6) SAE reporting procedures

SAEs should be reported from the time the subject signs the informed consent form until the 30th (including) calendar day after the last dose of study drug. If a serious adverse event occurs during the trial, it must be reported to the clinical supervisor and the principal investigator within 24 hours. At the same time, Serious Adverse Event (SAE) Report Form for Clinical Research must be filled out, signed and dated, and immediately reported to the sponsoring organization, the ethics committee of the research unit, CFDA, and the Food and Drug Administration of the region where the investigator is located (either provincial or municipal), in the form of a facsimile transmission.

Information on all SAEs must be recorded on the SAE form. Serious adverse events occurring during the continuation period up to 30 days after the last dose must be reported. SAEs occurring after 30 days of the last dose are generally not reported unless they are suspected to be related to the study drug.

For SAEs, detailed observation and documentation of symptoms, severity, time of occurrence, time to management, measures taken, time and mode of follow-up, and regression should be documented. If the investigator believes that a serious adverse event is not related to the trial drug, but is potentially related to a study condition (e.g., discontinuation of the original treatment, or comorbidities during the course of the trial), this relationship should be detailed in the narrative section of the SAE on the medical record report form. If there is a change in the intensity of an ongoing SAE or its relationship to the subject drug, a serious adverse event follow-up report should be sent to the sponsor immediately. All SAEs should be followed until recovery or stabilization.

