- [17] Adverse events: recorded from the time of signing the informed consent to 90 days after the last dose. Adverse events should be followed until they disappear, resolve to baseline levels or  $\leq$  grade 1, reach steady state, or are reasonably explained (e.g., lost to follow-up, death).
- [18] Concomitant medications: record drug combination/concomitant treatments within 14 days prior to the first study medication up to the end of the safety visit, and record drug combination/concomitant treatments only for adverse events related to the use of the study drug after completion of treatment with the study drug or withdrawal from the study.
- [19] Safety follow-up: starting after the last study treatment, follow-up visits will be conducted every 30 days ( $\pm 3$  days) until 90 ( $\pm 7$  days) after the last study treatment. The first of these safety visits should be at the study center to complete the examinations and assessments specified in the protocol; subsequent safety follow-ups will be by telephone and will be required only to collect survival information, drug combination/concomitant therapies, and adverse events.
- [20] Survival follow-up: at the end of the safety follow-up period, subjects are entered into survival follow-up until the subject dies, is lost to follow-up, informed consent is withdrawn, or the sponsor terminates the study. During this period, follow-up visits were conducted every 3 months during years 1-2, every 6 months during years 3-5, and annually thereafter to collect survival information as well as information on subsequent treatment.

- [21] Myocardial enzymes test: creatine kinase isoenzyme (CK-MB), alpha-hydroxybutyrate dehydrogenase, creatine kinase, lactate dehydrogenase, etc., once within 7 days prior to randomization as well as pre-dose, pre-operative, post-operative, and safety follow up for the second and third cycle of the drug; supplemental testing will be performed during the study period in the presence of precordial pain, palpitations, and electrocardiographic abnormalities, as well as at the end of the treatment.
- [22] Drug of this study: sintilimab, anlotinib in combination with chemotherapy; see the study dosing section for a detailed description.

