## **4. Research procedures and data collection**

### **4.1 Data collection program**

The duration of safety data collection spans from the time the patient signs the Informed Consent Form (ICF) until 30 days after the final dose. All adverse events must be documented in the Case Report Form (CRF) from the moment the ICF is signed until the study concludes. The incidence and severity of adverse events will be observed and assessed according to the NCI-CTCAE 5.0 criteria. Each patient will undergo scheduled visits, and specific data will be recorded at various time points during these visits.

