#### **4.4 Radical surgery**

Within 4-6 weeks (22-42 days) of the last dose, the radical surgery was performed.

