## **6. Adverse event reporting**

### **6.1 Adverse event observation**

An adverse event (AE) is any unfavorable medical occurrence that happens after a subject in a clinical trial has signed an informed consent form, regardless of whether it is causally related to the treatment. AEs can encompass a wide range of unfavorable symptoms, signs, laboratory test abnormalities, or diseases. Specifically, AEs include at least the following:

- 1) A pre-existing medical condition or disease is recorded as an AE only if it worsens after the initiation of study treatment.

2) Any newly occurring AE: This includes any new adverse medical condition (such as symptoms, signs, or newly diagnosed diseases).

3) Abnormal clinically significant laboratory test results that are not attributable to concomitant diseases.

Adverse events that occur during both the pre-treatment and post-treatment phases are also considered AEs according to regulations. Therefore, safety monitoring for AEs or serious adverse events (SAEs) should be reported from the time the subject enters the trial (by signing the informed consent form) until the end-of-trial visit.

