## **6.3 AE record**

Detailed records of the name, severity, time of occurrence, duration, management measures, and resolution of various adverse events (AEs) during the study period will be meticulously documented in the case report form (CRF). Related examinations will

be conducted at least once a week and followed up until normalization or the end of the study. Any adverse events occurring within 30 days of the last dose should be reported and recorded.

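### AE and SAE collection ends at 30 days, 90 days or study end depending on the section, so the co-primary safety endpoint has no fixed window around surgery

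*Protocol*

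**What the plan says.** The protocol states the end of AE and SAE collection in several places.

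- **30 days after the last dose.** Section 4.1, first sentence, collects safety data "until 30 days after the final dose". Section 6.3: "Any adverse events occurring within 30 days of the last dose should be reported and recorded". Section 6.5(6), for SAEs: "SAEs should be reported from the time the subject signs the informed consent form until the 30th (including) calendar day after the last dose", followed by "SAEs occurring after 30 days of the last dose are generally not reported unless they are suspected to be related to the study drug".
- **90 days after the last dose.** Flow chart note [17] has AEs "recorded from the time of signing the informed consent to 90 days after the last dose". Note [19] schedules safety contacts every 30 days up to day 90.
- **End of study.** Section 4.1, second sentence: "All adverse events must be documented in the Case Report Form (CRF) from the moment the ICF is signed until the study concludes". Section 6.1 carries both AEs and SAEs "until the end-of-trial visit".
- **No end date.** Section 4.8 continues to look for new AEs after the last dose and sets no limit.

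On surgery, section 4.4 says: "Within 4-6 weeks (22-42 days) of the last dose, the radical surgery was performed". Section 3.2 makes safety a primary endpoint alongside pCR. It covers all AEs, with no time window, and names hemorrhage and immune-associated pneumonia among the events of special interest. Section 5.1.1 lists the incidence of SAEs and of deaths among the safety variables. Section 6.7 grades postoperative complications by Clavien-Dindo, without a window. Section 4.5 mentions up to 13 cycles of adjuvant sintilimab as standard care.

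**The concern.** An incidence needs a defined period at risk, and here the period differs by section. Section 4.1 contradicts itself in consecutive sentences. The shortest window, 30 days, ends close to the planned operation, so the choice of section decides whether the postoperative course is inside or outside a primary endpoint.

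SAEs judged unrelated to study drug are the most exposed. A site following 6.5(6) would generally not report a serious postoperative bleed or pneumonia on day 35 that it attributed to the operation. A site following 6.1 would report it. In a single-arm trial there is no control group against which to check that attribution. Section 3.4 names two hospitals, and if they follow different sections their rates are not comparable and should not be pooled. A statistical analysis plan cannot repair this afterwards, because it cannot recover events that sites were told not to collect.

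**Working it through.** The plan derives no figure here that could be reproduced. The check is a day count from its own windows.

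**Inputs.** SAE limit: day 30 (6.5(6)). AE limit in the flow chart: day 90 (note [17]). Surgery: days 22 to 42 (4.4), also written there as 4-6 weeks. Postoperative visit: 3-6 weeks after surgery (flow chart). All are first counted from the same last dose.

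**Step 1: can the end dates be reconciled as AE versus SAE rules?** A split of 90 days for AEs and 30 days for SAEs would be coherent, but the text does not support it. Sections 4.1 and 6.3 apply 30 days to safety data and AEs in general, while 6.1 carries SAEs to the end-of-trial visit.

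**Step 2: 30-day limit against surgery on days 22-42.**
- Permitted surgery days: 42 − 22 + 1 = 21.
- Days after the limit (31 to 42): 42 − 31 + 1 = 12, and 12/21 = 57%.
- On the other 21 − 12 = 9 days, the postoperative time inside the window runs from 30 − 30 = 0 to 30 − 22 = 8 days.
- If every permitted day is weighted equally (an assumption), the share of the first 30 postoperative days covered is (0 + 1 + … + 8)/(21 × 30) = 36/630 = 5.7%.

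**Step 3: sensitivity.**
- *Surgery read literally as 4-6 weeks (days 28-42).* There are 42 − 28 + 1 = 15 permitted days, of which 12 (80%) fall after the limit. At most 30 − 28 = 2 postoperative days remain. Coverage is (0 + 1 + 2)/(15 × 30) = 0.7%.
- *Two clocks.* Suppose the SAE clock starts at the last anlotinib capsule (cycle 3 day 14) and the surgery clock at the last infusion (cycle 3 day 1). The limit is then cycle day 14 + 30 = 44, and surgery falls on cycle days 1 + 22 = 23 to 1 + 42 = 43. That leaves 44 − 43 = 1 to 44 − 23 = 21 postoperative days. The answer therefore changes with a definition that the protocol does not give.

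**Step 4: the flow chart's 90-day limit.** Postoperative days covered: 90 − 42 = 48 to 90 − 22 = 68. No permitted surgery day falls outside, and the first 30 postoperative days are always covered.

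**Step 5: the postoperative visit.** It falls nominally between day 22 + 21 = 43 and day 42 + 42 = 84. The flow chart therefore asks for AEs at a visit that always lies beyond the 30-day limit and within 90 days.

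**The case against.** The strongest reply is that the broader instructions exist and should prevail. The flow chart asks for AEs before surgery, 3-6 weeks after it and during follow-up. Sections 4.1 (second sentence) and 6.1 run to the end of the study, 4.8 keeps looking for new AEs, and 6.7 grades postoperative complications. Section 6.5(6) mainly concerns expedited notification, which need not limit what is entered in the CRF, and it keeps SAEs suspected to be drug-related reportable after day 30.

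Much of this stands, and it rules out three stronger readings that a reader might infer.

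- *That perioperative harm is missing from the primary safety endpoint.* This would follow only if the 30-day sections overrode the rest, and nothing says that they do.
- *That postoperative deaths are lost.* Deaths are a separate safety item in 5.1.1, are recorded at survival visits (4.7) and count in OS (5.1.2).
- *That the limit precedes most operations.* The figure of 12 in 21 is a share of permitted days. The protocol gives no distribution of surgery dates.

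It might also be argued that adjuvant sintilimab pushes the last dose far beyond surgery. That reading is weak, because section 3.6.1 limits study treatment to three cycles and 4.5 calls the adjuvant cycles standard care. The neoadjuvant reading is the natural one, but it is not written down.

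The reply does not remove the conflict. Nothing says that the broader instructions prevail either, and the 30-day rule in 4.1 and 6.3 concerns collection and recording, not only notification. Clavien-Dindo grading does not fill the gap, since it has no window and is not listed among the endpoints in 3.2, 3.3 or 5.1.

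**Conclusion.** The point holds as an internal contradiction that leaves a co-primary endpoint without a fixed window. It does not show that perioperative events will be lost. Three incompatible end dates are stated, and the clock they run from is undefined. With a single last dose and surgery on days 22-42, the 30-day limit falls before 12 of 21 permitted days and leaves 0 to 8 postoperative days on the rest. With two different clocks it leaves 1 to 21 days. With the flow chart's own 90 days it leaves 48 to 68.

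Whether perioperative events enter the safety results, above all SAEs judged unrelated to study drug, therefore depends on which section a site follows. The pCR analysis is not affected. The contradiction should be resolved in the protocol, because it governs what sites collect.

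**What to change.** 1. Reconcile 4.1, 4.8, 6.1, 6.3, 6.5(4), 6.5(6) and flow chart note [17] to one AE and SAE collection window for the primary safety endpoint that always spans the postoperative period. An example is consent to at least 90 days after the last neoadjuvant dose, which is the flow chart's own schedule, or to 30 days after surgery if surgery is delayed. Within the planned window the second limb is inactive (42 + 30 = 72, below 90). It takes effect only for surgery after day 90 − 30 = 60.
2. Remove the 30-day cut-offs as limits on collection. If a shorter limit is wanted for expedited notification only, label it as such.
3. Define the last dose as the last neoadjuvant study dose and name the drug that starts the clock. Reconcile 4-6 weeks with 22-42 days, which differ at the lower end (28 against 22 days).
4. Section 6.5(4) ends reporting of non-death AEs when another antitumor therapy starts. State how this applies within the window, including to adjuvant sintilimab.
5. State whether Clavien-Dindo complications (6.7) count in the safety endpoint.
6. If events during adjuvant sintilimab are collected, as the study-end wording in 4.1 and 6.1 implies, give them their own window and tabulate them separately.

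The cost is amendment wording and some extra SAE forms. Contacts to day 90 are already scheduled in note [19].

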## **6.6 irAE**

Immune-related adverse events (irAE) are specific events (including: pneumonia, diarrhea/colitis, hepatitis, nephritis/renal dysfunction, rash, and endocrinopathies) for which subjects received immunosuppressive medications for treatment. Endocrine events (hypothyroidism/thyroiditis, hyperthyroidism, pituitary gland inflammation,

diabetes mellitus, adrenal insufficiency) are usually exceptions because these endocrine events are generally not related to treatment and can usually be managed without immunosuppressive interventions. Preferred terms used to support the warnings and precautions included in irAE analysis are shown in the table below:

| irAE category            | Terms included under irAE category (MedDRA codes)                                                                            |
|---------------------------------|-------------------------------------------------------------------------------------------------------------------------------------|
| Pneumonitis                     | Pneumonitis, interstitial pneumonitis                                                                                               |
| Diarrhea/Colitis                | Diarrhea, colitis, enterocolitis                                                                                                    |
| Hepatitis                       | Hepatotoxicity, hepatitis, acute hepatitis, autoimmune hepatitis, elevated AST, elevated ALT, elevated bilirubin, elevated ALP      |
| Adrenal Insufficiency           | Adrenal insufficiency                                                                                                               |
| Hypothyroidism/Thyroiditis      | Acute thyroiditis (collapse with the frequency of thyroiditis), autoimmune thyroiditis (collapse with the frequency of thyroiditis) |
| Hyperthyroidism                 | Hyperthyroidism                                                                                                                     |
| Pituitary gland inflammation    | Pituitary gland inflammation                                                                                                        |
| Diabetes                        | Diabetes, diabetic ketoacidosis                                                                                                     |
| Nephritis and renal dysfunction | Nephritis, acute nephritis, tubulointerstitial nephritis, acute renal failure, renal failure, elevated creatinine                   |
| Rash                            | Rash, maculopapule                                                                                                                  |

## 6.7 Postoperative complication

Postoperative complications were evaluated using the Clavien – Dindo Classification of Surgical Complications.

## 7. Quality control and quality assurance

Personnel participating in this study, including clinicians and supervisors, will be rigorously trained to ensure that the trial is performed in accordance with the clinical study protocol, to protect the safety and rights of the subjects, to follow standard operating procedures, and to correctly and completely record and report study data.

## **8. Ethical, regulatory and administrative principles**

### **8.1 Ethical principles**

This study will be conducted in accordance with the principles established by the 18th Joint World Medical Association Congress (Helsinki, 1964) and all subsequent revisions.

### **8.2 Laws and regulations**

This study will be conducted in compliance with relevant national laws and regulations and the current GCP guidelines of the CFDA.

### **8.3 Data protection**

Personal data of patients and personal data of investigators that may be included in the Company's database shall be handled in accordance with relevant national laws and regulations. When archiving or processing personal data related to investigators and/or patients, care must be taken to protect the privacy of individuals and appropriate measures must be taken to protect and prevent any unauthorized third parties from accessing such data.

## **9. Revised program**

Amendments to the study protocol must be discussed and agreed by the scientific committee and signed by the principal investigator and the sponsor. Important modifications and changes must be reported to the ethics committee of the group leader unit for review and agreement to the revised version in writing.

